## Abstract

**Background:**

Childhood overweight and obesity is a serious public health issue with an increase being observed in preschool-aged children. Treating childhood obesity is difficult and few countries use standardized treatments. Therefore, there is a need to find effective approaches that are feasible for both health care providers and families. Thus, the overall aim of this study is to assess the acceptance and effectiveness of a parent support program (the More and Less, ML) for the management of overweight and obesity followed by a mobile health (mHealth) program (the MINISTOP application) in a socially diverse population of families.

**Methods/design:**

A two-arm, parallel design randomized controlled trial in 300 2-to 6-year-old children with overweight and obesity from Romania, Spain and Sweden (*n* = 100 from each). Following baseline assessments children are randomized into the intervention or control group in a 1:1 ratio. The intervention, the ML program, consists of 10-weekly group sessions which focus on evidence-based parenting practices, followed by the previously validated MINISTOP application for 6-months to support healthy eating and physical activity behaviors. The primary outcome is change in body mass index (BMI) z-score after 9-months and secondary outcomes include: waist circumference, eating behavior (Child Eating Behavior Questionnaire), parenting behavior (Comprehensive Feeding Practices Questionnaire), physical activity (ActiGraph wGT3x-BT), dietary patterns (based on metabolic markers from urine and 24 h dietary recalls), epigenetic and gut hormones (fasting blood samples), and the overall acceptance of the overweight and obesity management in young children (semi-structured interviews). Outcomes are measured at baseline and after: 10-weeks (only BMI z-score, waist circumference), 9-months (all outcomes), 15- and 21-months (all outcomes except physical activity, dietary patterns, epigenetics and gut hormones) post-baseline.

**Discussion:**

This study will evaluate a parent support program for weight management in young children in three European countries. To boost the effect of the ML program the families will be supported by an app for 6-months. If the program is found to be effective, it has the potential to be implemented into routine care to reduce overweight and obesity in young children and the app could prove to be a viable option for sustained effects of the care provided.

**Trial registration:**

ClinicalTrials.gov NCT03800823; 11 Jan 2019.

## Background

According to the World Health Organization childhood obesity is one of the gravest public health challenges of today’s society [1], with approximately 108 million 2- to 19-year-old children being classified as having obesity [2]. More specifically, in children less than 5 years, there has been a swift increase in childhood overweight and obesity and if these trends continue it is predicted that 70 million children will be overweight or obese by 2025 [3]. These statistics are concerning as Geserick et al. [4] found that 90% of 3 year olds with obesity still had overweight or obesity in adolescence. Furthermore, for those adolescents with overweight or obesity, the majority of weight gain happened between two and 6 years of age [4]. Thus, this demonstrates the need for evidence-based treatment programs in the pre-school years in order to attempt to rectify the increased prevalence of childhood overweight and obesity.

According to Colquitt et al. [5] for children under 6 years of age multicomponent interventions (i.e., diet, physical activity, and behavioral interventions) seem to be effective at treating overweight and obesity. However, the authors did state that evidence is limited [5]. To date, the majority of the treatment interventions for overweight and obesity use face-to-face delivery methods [6]. A recent meta-analysis by Ling et al. [6] found small effect sizes on treatment interventions for preschool-aged children for body mass index (BMI) (− 0.28 kg/m^2^, *p* < 0.001) using various in person delivery methods. Furthermore, the More and Less (ML) study found that at the 12-month follow-up, a 10-week group treatment program focusing on parenting practices had a greater reduction in BMI z-scores than standard treatment in health care (− 0.30 vs. -0.07, *p* < 0.05). An even greater reduction was observed in the intervention group who received booster sessions (a 30-min phone call every 4 to 6 weeks over a 9-month period) [7]. These results are promising; however, sustained contacts with families after treatment programs are burdensome on both health care providers and participants, which makes it difficult to scale-up. Therefore, different types of boosters need to be used in order to reduce the burden on both health care and participants.

The universal use of smartphones makes the use of mobile health (mHealth) an option for boosting the effects of treatment programs. mHealth is increasingly being used for promoting healthy habits and as treatment of many types of health conditions and diseases. In adults, two meta-analyses have found that mHealth interventions focusing on weight loss significantly decreased participants’ weight in the intervention groups compared to the control groups [8, 9]. In children and adolescents few studies have utilized mHealth in the prevention or treatment of obesity [10–14] and hardly any have been conducted in the preschool-age group [15, 16]. The Mobile-based Intervention Intended to Stop Obesity in Preschoolers (MINISTOP) trial was a mHealth obesity prevention intervention that was developed and led by [name] and her team to improve 4-year-old children’s body composition, dietary, physical activity, and sedentary behaviors [17, 18]. The MINISTOP intervention had a significant effect on a composite score composed of body composition, diet, and physical activity variables, with this effect being more evident among children with a higher fat mass index [18]. There are numerous advantages of mHealth over conventional intervention approaches such as: the programs can be delivered any time and place; are interactive; can be tailored to different groups (e.g., translated into multiple languages); and reduces burden on health care professionals and participants. These advantages further motivates the use of mHealth in families with young children with overweight and obesity.

The mechanisms that drive weight gain such as epigenetics and gut hormones are still unclear [19, 20]. Epigenetics has received attention during the recent years for the putative involvement in transmitting obesity risk to offspring and in the heritable regulation of gene expression without altering their coding sequence [21]. The most relevant epigenetic mechanisms involved in gene activity control are histone modifications, non-coding RNAs (ncRNA) and DNA methylation [20]. Further, obesity has been associated with the epigenetic modulation of several genes. For example, a relationship has been reported between increased BMI and adiposity as well as higher DNA methylation levels at the hypoxia-inducible transcription factor 3A (HIF3A) gene [22]. Moreover, an increased methylation in the gene RXRA measured at birth has been associated with greater adiposity in later childhood [23]. Two other investigations identified a strong correlation between obesity and serum levels of micro RNA (miR)-122 and miR-519d [24] and found DNA methylation to be related to insulin resistance [25]. However, these findings need to be confirmed and further explored in young children.

Another field of interest for obesity is the gastrointestinal tract (GIT) [26]. The GIT plays an important role in acute appetite regulation through a number of mechanisms: (1) the release of hormones that play a role in appetite regulation such as anorectic hormones (Peptide YY, PYY, and glucagon-like peptide, GLP-1) and orexogenic gut hormones (e.g., ghrelin), (2) the enteric nervous system and signals through the vagus to the brain to influence appetite and (3) secondary to stimulating signals from other organs such as liver adipose. Previous research in adults has demonstrated that the infusion of the GIT anorectic hormones PYY and GLP-1 at physiological doses has profound effects to suppress appetite [26]. Also weight loss appears to lead to a suppression of PYY and GLP-1 suggesting a role in the feelings of hunger during weight reduction. However, evidence of the role of GIT hormones in overweight and obesity among young children is sparse.

A major challenge in the management of obesity in both adults and children is understanding what people eat. Most dietary assessment methodologies use methods of self-reported food intake which is a subject to large misreporting error [27, 28]. It is therefore impossible to understand what children eat. Garcia et al. has developed a new metabolomic methodology of dietary assessment using urine, which is not subject to the same misreporting errors [29]. This method has been validated in adults. Our aim is to do this is children.

To the best of our knowledge there is no study to date that has the ambition to assess a broad array of key biological and social determinants of obesity in young children. This study protocol outlines the design of a multi-country study that incorporates both a parent support program and mHealth in an overweight and obesity intervention in 2- to 6-year-old children with overweight and obesity.

### Aim

The overall aim of this study is to assess the feasibility, acceptance and effectiveness of an overweight and obesity intervention in a socially diverse population of families. The specific aims are:To determine the effectiveness on child weight status (BMI z-score) of a 10-week parent support program delivered in groups focusing on evidence-based parenting practices (the ML program) followed by a mHealth component for 6-months (the MINISTOP application, app) for overweight and obesity in preschool-aged children.To assess change in secondary outcomes, which are: waist circumference, child eating behavior, parental feeding practices, and physical activity.To assess epigenetic mechanisms and physio pathological processes underlying childhood obesity including the role of gut hormones.To assess and validate child food intake with metabolic markers in urine metabolomics.To evaluate the feasibility of recruitment (facilitators and barriers), attrition and acceptability of the ML program, the standard treatment and the overall acceptance of overweight and obesity management according to patients and care providers.

### Hypotheses

Our central hypothesis is that the intervention (the ML program followed by the MINISTOP app for boosting) will be more effective in decreasing children’s BMI z-score (primary outcome), improving eating and feeding behaviors, and physical activity (secondary outcomes) compared to standard care. Another study hypothesis is that the intervention will produce changes in urinary metabolites, which will serve as biomarkers of the nutritional outcomes or as targets for application. We also hypothesize that the parent program and the mHealth intervention will be well accepted by families and caregivers.

## Methods

### Study design

ML Europe is a two-arm parallel design randomized controlled trial (RCT) comparing overweight and obesity treatments in 2-to 6-year-old children in three countries (Romania, Spain, and Sweden). Following baseline assessments, participants will be randomized into the intervention and control group in a 1:1 ratio. The intervention group receives a 10-week parent support program (the ML program) which focuses on evidence-based parenting practices [7, 30] followed by a previously validated 6-month mHealth program (the MINISTOP app, PI: [name]) to support healthy lifestyle changes [17, 18]. The control group receives standard treatment as offered in the country of participation. The different interventions are described in greater detail below. Assessments will be conducted at 10 weeks, 9 months, 15 months, and 21 months post-baseline (see Fig. 1 for study outline). This study protocol follows the SPIRIT 2013 statement [31, 32].

**Fig. 1 Fig1:**
[figure not shown]
Flow-chart of the More and Less Europe trial design

### Sample size and power calculation

Based on power calculations, 75 children are needed in each group (adjusted for drop-out) to detect a difference of 0.3 BMI z-score with 85% power at the 9-month follow-up between the intervention and control group. These calculations are based on a previous study in this age group [33]. Thus, each site aims to recruit 100 participants to ensure adequate power.

### Participants, eligibility, and recruitment

In total, we aim to include 300 families (*n* = 100 in Romania, Spain, and Sweden, respectively). To be included in this study: children must be between 2 and 6 years old and have overweight or obesity as classified by international cut-offs [34]; have no other underlying medical condition(s); the child has not started any treatment for overweight or obesity; and at least one parent has to have the ability to communicate in Romanian, Spanish, or Swedish depending on the country of participation. Parents who do not own a smartphone compatible with the MINISTOP app will be excluded from this study (i.e., version 10.0 or higher for iOS or version 5.0 or higher for Android).

Recruitment will follow a standardized protocol for all countries. In Romania, family physicians and pediatricians will be involved to hand out information regarding the study to families with 2- to 6-year-olds with overweight or obesity. Parents who want to learn more about the study are provided with a phone number, email address, web page and Facebook page with information of how to contact the research group. Participants will also be recruited, as self-referrals, using an official page for the study on Facebook to be shared with specialized groups.

In Spain, families with children who attend weight and height assessments at their pediatricians at primary care health centers and hospitals will be asked to participate in the study. If the parents are interested in participating, the pediatrician will schedule a visit within a maximum of 7 days to provide them with more detailed information regarding the study and for them to sign the informed consent.

Finally, in Sweden, the recruitment methods have been previously described in detail [7, 30]. Briefly, recruitment is done primarily at primary child health care centers, where all parents of children from birth to 5 years of age are offered free, yearly check-ups. If overweight or obesity is detected the nurse provides a verbal and a short one-page explanation of the study. If the parent(s) are interested in participating the nurse sends a referral to the research group that will send out more detailed information regarding the study together with a consent letter. After 1 week, a member from the research team will contact the families to answer any questions that they have. Recruitment is also conducted at secondary health care (i.e., out-patient pediatric clinics). Additionally, self-recruitment is being done through newspaper ads as well as by placing posters on primary health care bulletin boards.

For all countries, after fully informing the families, if they still want to participate they send back the signed consent letter, which is subsequently signed by a member of the research team and a copy is sent back to the family. A time for baseline assessments is then scheduled with the research group.

### Randomization and blinding

After the consent form has been signed, the participants are randomly allocated to either the intervention group (parent support program and mHealth booster) or the control group (standard care as per country) at a 1:1 ratio via a random allocation sequence list (in blocks of three). The sequence list was generated using free software environment for statistical computing and graphics R (version 3.5.1) [35]. The random allocation sequence is managed by a person who has no relationship with recruitment or treatment and opaque envelopes are used to ensure concealment. Those assessing the outcomes are blinded to the treatment allocation; however, owing to the nature of the intervention participants are not blind to their allocation.

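### The stated block size of three is inconsistent with 1:1 allocation to two arms; the effect on power is small, but the list must be checked and the sentence corrected

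*Protocol article*

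**What the plan says.** Under Study design, the protocol article describes a parallel trial with two arms in which "participants will be randomized into the intervention and control group in a 1:1 ratio". The abstract gives the same ratio.

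The method is under Randomization and blinding: allocation is "at a 1:1 ratio via a random allocation sequence list (in blocks of three"). The same paragraph adds that "The sequence list was generated using free software environment for statistical computing and graphics R (version 3.5.1"). It says that someone independent of recruitment and treatment manages the sequence, that opaque envelopes conceal it, and that outcome assessors are blinded.

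Three is the only block size given. The article states no varying sizes, no rule pairing blocks of opposite composition and no other meaning of three, such as three per arm. It does not say whether there is one list or one per country.

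Under Sample size and power calculation, "75 children are needed in each group (adjusted for drop-out") "to detect a difference of 0.3 BMI z-score with 85% power at the 9-month follow-up". The recruitment target is 300 families, 100 per country.

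**The concern.** In a permuted-block list for two arms at 1:1, each block holds equal numbers of both arms, so the block size must be even. Three is odd. The sentence therefore pairs a ratio with a block size that cannot deliver it within any block, and a reader cannot tell what the list contains. It could be a constant 2:1 list, a random mix of 2:1 and 1:2 blocks, or a list with an even block size that has been misdescribed.

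At stake are the true allocation ratio, the control of arm sizes that blocking is meant to give, and the accuracy of the published account of the randomisation. This is not a detail left to a fuller document. The article chose to state the block size, and the size conflicts with the ratio in the same sentence.

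**Working it through.** **Inputs from the article.** Two arms; ratio 1:1; block size 3; 300 children, 100 per country; 75 per group (with drop-out allowed for) for a difference of 0.3 at 85% power. The standard deviation, drop-out rate and alpha are not given. I assume a two-sided alpha of 0.05 and show the one-sided result as a range.

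**Step 1. Can the stated scheme be reproduced?** A block of three can split 0:3, 1:2, 2:1 or 3:0. None is equal. The ratio 1:1 needs a block size divisible by 1 + 1 = 2. Also, 100 = 33 × 3 + 1, so a site of 100 does not fill whole blocks of three. The stated combination is not reproduced.

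**Step 2. Every block with the same 2:1 composition.**
- Arm sizes: 300/3 = 100 blocks, giving 200:100.
- Variance ratio against 150:150: (1/200 + 1/100)/(1/150 + 1/150) = 0.0150/0.01333 = 1.125, an increase of 12.5%.
- The plan's 85% at 75 per group corresponds to a standardised effect of 1.960 + 1.036 = 2.996. With no drop-out this implies SD = (0.3/2.996) × √(75/2) = 0.613. Drop-out of 20% would imply 0.548, and 30% would imply 0.513. If the same drop-out applies throughout, it cancels from the power figures below.
- At 150:150 the standardised effect is 2.996 × √2 = 4.237. Power = Φ(4.237 − 1.960) = Φ(2.277) = 98.9%.
- At 200:100 it is 4.237/√1.125 = 3.995. Power = Φ(3.995 − 1.960) = Φ(2.035) = 97.9%.
- One-sided 0.05 instead: (1.645 + 1.036) × √2 = 3.792, power Φ(2.147) = 98.4%; then 3.792/√1.125 = 3.575, power Φ(1.930) = 97.3%.

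Either way the loss is about one percentage point.

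**Step 3. Majority arm chosen at random in each block (probability 1/2).** Each complete block adds +1 or −1 to the difference in arm sizes, so after b blocks the difference has mean 0 and SD √b.
- All 300 children, one list: b = 100, SD = 10. From the binomial distribution, P(exact balance) = 0.08, P(difference ≥ 10) = 0.37 and P(difference ≥ 20) = 0.057.
- One site, if each country has its own list (an assumption): b = 33 (99 children), SD = √33 = 5.7. The difference is odd, so it is never zero at that point.
- At 100 children, the 100th moves the difference by ±1 with equal chance. P(difference ≥ 10) = P(|D| ≥ 11) + ½ P(|D| = 9), where D is the difference after 33 blocks. P(|D| ≥ 11) = 0.080 and P(|D| = 9) = 2 × C(33,12)/2³³ = 0.083. The sum is 0.080 + 0.041 = 0.121, about a 12% chance of 55:45 or worse.
- Power hardly moves: at 160:140 it is 98.8%, against 98.9% at 150:150.

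**Step 4. Even blocks for comparison.** Blocks of 2 or 4 balance within every block and divide both 100 and 300. Blocks of 6 divide 300 but leave 4 over at 100. The difference within a list never exceeds half a block, so it is at most 3 for blocks of 6.

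**The case against.** The strongest reply is that the sentence is loose but the trial is sound. A list exists, because the article says that it was generated. The defect may lie only in the reported block size. Independent management of the sequence, opaque envelopes and blinded assessors are described separately and do not depend on the block size. Unequal arms cost precision; they do not by themselves bias the comparison. Both arms exceed the 75 required even at 200:100. Random mixing of 2:1 and 1:2 blocks still controls arm sizes better than simple randomisation, whose difference at 300 children has an SD of √300 = 17.3 against 10. A constant 2:1 list is also the less likely reading, because the article states 1:1 repeatedly.

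All of this stands as to size. It does not remove the inconsistency, since no reading of the text makes a block of three balanced.

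It also rules out four stronger readings that a reader might infer:
- **That no 1:1 list can be made from blocks of three.** Mixed blocks give 1:1 in expectation, and alternating 2:1 and 1:2 blocks would give it overall. What is impossible is balance within a block, and no pairing rule is stated.
- **That power falls from 85% to about 80.6%.** That figure belongs to 150 children split 100:50: Φ(2.996/√1.125 − 1.960). The trial plans 300.
- **That randomisation cannot be carried out or has failed.** The text shows only that the list is misdescribed or badly blocked.
- **That the group sessions are disrupted.** The article gives no group size and no required number of intervention families.

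**Conclusion.** The point holds as an internal inconsistency: two arms at 1:1 and blocks of three do not fit together, and nothing in the article reconciles them. The statistical consequence is small at the planned size. It is about one percentage point of power in the worst case (200:100), and almost nothing if 2:1 and 1:2 blocks were mixed at random.

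The power figures rest on an assumed alpha and on the plan's own 75 per group at 85%. The random-mix figures rest on a majority arm chosen with probability 1/2, and the per-site figures also on separate country lists. What matters more than power is that the actual ratio and blocking cannot be established from the text, although recruitment had begun in all three countries by February 2019. A correction is needed, but the documents do not support a claim that the comparison is biased or underpowered for this reason.

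**What to change.** First inspect the generated R list; nothing in the allocation should change before that.

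- If the list uses an even block size (for example three per arm, that is six), correct the sentence to that size.
- If it really uses blocks of three, keep the allocations already made and generate the unused part with even-sized permuted blocks, preferably with a separate list per country. Report how many children were allocated under the old list and the achieved ratio.
- In either case, state whether the list is single or by country.

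The first case costs one sentence. The second also costs a regenerated remainder of the list and new envelopes. Neither adds participants.
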